### Sample size calculation

The estimated sample size was calculated considering previous DHI and DGI (primary outcomes) results based on a previously published trial
[25], which compared VR outcomes in young versus older adults with vestibular disorders. The *t* test was used to detect clinical difference between means of continuous variants (primary outcomes) with 80% power, and 5% significance level. Estimations indicated that 34 individuals were required for the DGI (effect size = 2.5; standard deviation = 3.5) and 32 individuals for the DHI assessments (effect size = 14; standard deviation = 20), where effect size is the mean difference expected between the two groups and standard deviation is for the population. Hence, a minimum of 68 patients will be necessary for the sample. To minimize the effects of the dropout rate, at least 15% more individuals will be required to compose the final sample.

### Interventions

Interventions will be performed according to two distinct VR protocols (conventional Cawthorne&Cooksey and multimodal Cawthorne&Cooksey) conducted in the Otoneurology outpatient clinic. The VRs will be provided by two physiotherapists experienced in balance rehabilitation of older individuals and trained to standardize the VR protocols.

The control group will receive an active treatment, since scientific benefits of VR are already in evidence. In this case, placebo or nontreatment groups are not ethically advisable
[45]. The control group subjects will thus be treated according to the conventional Cawthorne&Cooksey VR protocol
[46-48], and the intervention group will be submitted to a novel protocol that includes multiple components to the conventional one.

The VR protocols will be provided in individual 50-minute sessions, twice a week, for 2 months (a total of 16 sessions). Under the condition of nonattendance, the session will be rescheduled to be performed in the same week. In the event of three (random or consecutive) absences during treatment, the subject will be excluded from the research and regarded as a withdrawal. In each session, absences, adverse symptoms, falling events, dizziness status according to the visual analog scale, and home exercises control will be recorded.

Regardless of the group, the subjects will be advised to maintain their usual activities and additional medical treatments during the research period. At the first session of both protocols, the subjects will receive a booklet including general information about VR, dietary advice, fall prevention and home exercises. The home exercises should be performed daily and consist of head and eye movements, performed while lying down (seven exercises, 14 minutes) and sitting (seven exercises, 14 minutes) to assure the patients’ safety. Following the recommendations, the intervention protocols will be implemented according to the randomization procedure.

Basically, the conventional Cawthorne&Cooksey protocol consists of eye, head and trunk exercises aimed at stabilizing the eye, reducing dizziness and improving body balance. The standard protocol comprises four stages, including specific exercises performed while lying down, sitting, standing, and walking positions. Each movement must be performed considering individual tolerability and avoiding neurovegetative symptoms. Lying and sitting exercises will take 1 week each; and, subsequently, standing and walking exercises will be undertaken during the following 6 weeks (3 weeks each) until the end of the intervention.

The Cawthorne&Cooksey modified protocol maintains the same exercises as the standard protocol, and includes flexibility, cognition, sensory interaction and muscle strength components. These alterations aim to match the various features of the ageing process, which is not restricted to vestibular problems alone, and to combine activities with higher functional demands.

The protocols are fully detailed in Additional file
1. Examples of the differences between both protocols are depicted in Figure 
2.

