**Methods/design:**

A randomized, single-blind, controlled clinical trial with a 3 months follow-up period will be performed. The sample will be composed of older individuals with a clinical diagnosis of chronic dizziness resulting from vestibular disorders. The subjects will be evaluated at baseline, post-treatment and follow-up. Primary outcomes will be determined in accordance with the Dizziness Handicap Inventory (functional capacity) and the Dynamic Gait Index (body balance). Secondary outcomes include dizziness features, functional records, body balance control tests, and psychological information. The older individuals (minimum sample *n* = 68) will be randomized to either the conventional or multimodal Cawthorne&Cooksey protocols. The protocols will be performed during individual 50-minute sessions, twice a week, for 2 months (a total of 16 sessions). The outcomes of both protocols will be compared according to the intention-to-treat analysis.

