### Outcome measures

Older patients will be submitted to baseline assessment (prior to randomization), and will be retested at post-treatment (8 weeks) and follow-up (3 months). The primary outcome measure to evaluate functional capacity is the Dizziness Handicap Inventory (DHI), while body balance control will be assessed by the Dynamic Gait Index (DGI).

The DHI is a self-perceived instrument that evaluates the impact of dizziness and unsteadiness on the quality of life of patients with vestibular disorders
[12,23]. The questionnaire consists of 25 items, divided into a seven-item physical subscale, a nine-item emotional subscale and a nine-item functional subscale. The total score ranges from 0 points (no handicap) to 100 points (severe handicap). To analyze DHI results, the total score, the categorical cutoff score >60 points, which indicates severe handicap
[24], and a reduction in the score ≥18 points following treatment, which is considered significant improvement in the quality of life
[25], will all be used.

The DGI is a functional gait scale composed of eight items with varying walking demands (ordinary walking, walking at different speeds, walking with vertical and horizontal head turns, walking over and around objects, making a 180° turn, and stair climbing)
[26,27]. The total score ranges from 0 points (severe impairment) to 24 points (normal performance). To analyze DGI results, the total score, the categorical cutoff score <19 points for fall risk
[28] and an increase in the score ≥4 points to identify a significant improvement following treatment
[25] will be used.

Secondary outcome measures will include the following measures.

Dizziness features will be assessed using a visual analog scale, etiology (peripheral, central vestibular disorder, or both), time elapsed from the first occurrence, duration and frequency, and associated symptoms. Fall data will include the history of falls in the previous 6 months and fear of falling. Hand-grip strength (kg) will be assessed by the manual hydraulics dynamometer SAEHAN™ (SAEHAN Corporation, SH5001, Masan, South Korea).

The Activities-specific Balance Confidence Scale is a self-perceived measure of balance confidence in performing daily activities
[29], with the score ranging from 0% (no confidence) to 100% (complete confidence).

The Vestibular Disorders Activities of Daily Living Scale evaluates the self-perceived impact of vestibular impairment on daily activities

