### Statistical analysis

The effects of the VR protocols will be tested through both intention-to-treat and per-protocol analysis. For the intention-to-treat analysis, missing post-treatment or follow-up outcomes data will be replicated from previous measures available (assuming no change for noncompleters). For per-protocol analysis, data from excluded subjects will be disregarded for analysis. The groups will be compared at baseline by the chi-square test for qualitative data and by the *t* test for quantitative data. To analyze changes in outcomes at baseline, post-treatment, and follow-up between and within groups, analysis of variance with repeated measures will be applied. A normality test will be applied to the outcome measures; when data are not normally distributed, equivalent nonparametric tests will be used. Potential interactions between treatment and covariates, such as age, sex, comorbidities, medications, dizziness features, psychocognitive aspects, adherences and follow-up data, will also be tested. The results will be presented as frequencies/percentages for categorical variables, and as means, medians, standard deviations and 95% confidence intervals for continuous variables. Data analyses will be performed using SPSS for Windows version 17.0 (SPSS Inc., Chicago, IL, USA) and the significance value for all tests will be set at *P* <0.05.

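### Three absences exclude a participant from the research with no provision for later assessment, so for that subset the intention-to-treat comparison rests on copied baseline scores

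*Protocol article*

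**What the plan says.** - **Attendance rule (Interventions).** "In the event of three (random or consecutive) absences during treatment, the subject will be excluded from the research and regarded as a withdrawal". Treatment is 16 sessions over 2 months. The sentence just before the rule says: "Under the condition of nonattendance, the session will be rescheduled to be performed in the same week". The article does not say whether a session made up in this way still counts as an absence.
- **Assessments (Outcome measures and Table 1).** After baseline, participants "will be retested at post-treatment (8 weeks) and follow-up (3 months"). Both primary outcomes, DHI and DGI, are measured only at these three time points.
- **Analysis promise (Abstract).** "The outcomes of both protocols will be compared according to the intention-to-treat analysis". The Statistical analysis section widens this: "The effects of the VR protocols will be tested through both intention-to-treat and per-protocol analysis".
- **Missing data (Statistical analysis).** For intention-to-treat, "missing post-treatment or follow-up outcomes data will be replicated from previous measures available (assuming no change for noncompleters"). For the other set: "For per-protocol analysis, data from excluded subjects will be disregarded for analysis".
- **Status (Trial status).** The study ended by September 2012, with analysis and publication to follow in 2013.

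**The concern.** An intention-to-treat comparison needs outcomes from everyone randomised, including those who attend badly. This plan treats poor attendance as leaving the research, not only as non-adherence. Ordinary dropout is outside the sponsor's control; this loss is written into the protocol and may fall on people who would have come back to be assessed.

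Both analyses are affected. Intention-to-treat gives these participants a change of exactly zero. Per-protocol removes them and compares the better attenders in each arm. A separate analysis plan cannot repair this, because it cannot recover assessments that were never made. At stake are the size of the treatment difference on both primary outcomes, the power to detect it and, if exclusion differs between arms, its bias.

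**Working it through.** **1. What an excluded participant contributes.** Absences can only occur during the treatment period. The first post-baseline assessment is at its end, so baseline is the only DHI and DGI measurement held when the rule takes effect. Carrying forward the previous measure then puts baseline into both the 8-week and the 3-month cells.

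**2. The plan's own sample size.** Inputs from Sample size calculation: DGI difference 2.5, SD 3.5; DHI difference 14, SD 20; 80% power; 5% significance (two-sided assumed). The exact two-sample t test needs 31.76, so 32 per group, for DGI and 33.02, so 34 per group, for DHI. The larger figure doubled is 2 × 34 = 68, which reproduces the stated total. (The article attaches 34 to DGI and 32 to DHI; the total is unaffected.) Allowing for 15% loss gives 68 / 0.85 = 80, or 40 per arm. Adding 15% literally gives 68 × 1.15 = 78.2, so 79.

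**3. How many could be excluded.** The documents give no miss rate. Let *p* be the chance that a session becomes an absence that counts, independently across 16 sessions (assumption). Then P(3 or more) = 1 − Σ C(16,k) p^k (1−p)^(16−k), summed over k = 0, 1, 2.

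| Assumed *p* | P(3 or more of 16) |
|---|---|
| 3% | 0.011 |
| 5% | 0.043 |
| 8% | 0.131 |
| 10% | 0.211 |
| 15% | 0.439 |

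The unresolved make-up question decides which row applies. Suppose 10% of sessions are first missed. If made-up sessions still count, the result is 21%. If they do not count and half are made up, *p* is 10% × 0.5 = 5% and the result is 4.3%. If 70% are made up, *p* is 10% × 0.3 = 3% and the result is 1.1%.

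**4. Effect on power when exclusion is equal in both arms.** Let *w* be the share excluded. Those participants add no between-group difference, so the expected difference is δ(1 − w). At w = 15% this is 2.5 × 0.85 = 2.125 for DGI and 14 × 0.85 = 11.9 for DHI. The SD is taken as unchanged (assumption). Power of the two-sided t test with 40 per arm:

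| *w* | DGI | DHI |
|---|---|---|
| 0% | 0.884 | 0.871 |
| 5% | 0.850 | 0.836 |
| 10% | 0.810 | 0.795 |
| 15% | 0.765 | 0.748 |
| 20% | 0.714 | 0.696 |

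The normal approximation, Φ(δ(1 − w) / (σ√(2/40)) − 1.96), gives 0.775 and 0.758 at 15%, so about 0.77 and 0.75 is a fair summary. The 15% inflation replaces lost numbers; it does not restore the diluted difference.

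**5. Effect if exclusion differs by arm.** If excluded participants would have changed as much as the others, the bias is (within-group change) × (difference in exclusion shares). With an 18-point DHI change (the improvement threshold in Outcome measures) and assumed shares of 10% and 20%, it is 18 × 0.10 = 1.8 points, or 1.8 / 14 = 13% of the planned difference.

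**The case against.** The strongest reply is that the rule says nothing about assessments. Data from excluded participants are set aside explicitly only for per-protocol, and intention-to-treat fills in only what is missing. On that reading, the rule merely defines the per-protocol set. It is true that the article never states that assessments stop. But exclusion from the research, recorded as a withdrawal, is not how one describes a participant who stays in follow-up, and no sentence provides for that follow-up. At best, retention is not secured.

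Other objections limit the point, and these stand:

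- A reader might infer that the intention-to-treat analysis cannot be done. It can. Real post-baseline data are lacking only for the excluded subset; all other assessed participants contribute observed scores.
- A reader might infer that a 10% miss rate by itself uses up the 15% dropout allowance. That ignores same-week rescheduling and holds only if made-up sessions still count as absences, or if few are made up. The allowance is also stated as a minimum.
- A reader might picture the rule as mainly removing people who attended 13 of 16 sessions (13/16 = 81%). Without make-up sessions that is the ceiling, reached only when the third absence falls on session 16. Under the model above at 10%, this is C(15,2) × 0.1³ × 0.9¹³ / 0.211 = 13% of those excluded, and the mean number attended at exclusion is about 9.
- A reader might infer that the multimodal arm will lose more people. Its content is broader and more demanding, but the number, length and frequency of sessions are the same in both arms. No passage shows that attendance would differ.

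**Conclusion.** The concern holds in a limited form. The attendance rule and the intention-to-treat promise do not fit together: for participants with three absences, the plan provides no post-baseline measurement and substitutes an assumed zero change, while per-protocol omits them. The conflict follows from the text alone and needs no assumed rate.

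Its size does depend on assumptions. The excluded share could be about 1% or more than 20%, depending on a miss rate the documents do not give and a counting rule they do not state. If 15% were excluded equally, power would be about 0.77 for DGI and 0.75 for DHI with 40 per arm, below the stated 80%; at 5% it would stay above 80% for both. Bias from unequal exclusion is possible but not shown.

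The 0% row in the power table assumes that poor attenders, if measured, would show the full planned difference. They may not. The sure gain from assessing them is an estimate based on observed outcomes; a gain in power is only likely.

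**What to change.** In Interventions, replace the exclusion and withdrawal wording. State that a participant who reaches three absences is classed as non-adherent, stays in the trial for the 8-week and 3-month assessments, and is analysed in the randomised arm. Use the three-absence rule only to define the per-protocol set, and state whether a session made up in the same week counts as an absence. No position is taken here on whether treatment sessions continue.

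The cost is two already scheduled assessments per affected participant. With 80 randomised and the assumed 5% and 10% rates, that is 80 × 0.043 ≈ 3 to 80 × 0.211 ≈ 17 participants, some of whom may decline.

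Because the study has concluded, the change to data collection can no longer be made. The steps still open cost little:

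1. Use every assessment actually obtained from these participants in the intention-to-treat analysis.
2. Report the number excluded for absences in each arm, and how absences were counted.
3. Describe the intention-to-treat result as resting on imputed values for those without assessments.

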**Figure 2 F2:**
[figure not shown]
**Conventional and multimodal vestibular rehabilitation example of differences.** Stage D, Exercise A – throwing a ball: (**A**) conventional protocol and (**B**) multimodal protocol. Stage D, Exercise B – kicking a ball: (**C**) conventional protocol and (**D**) multimodal protocol.

### Statistical analysis

The effects of the VR protocols will be tested through both intention-to-treat and per-protocol analysis. For the intention-to-treat analysis, missing post-treatment or follow-up outcomes data will be replicated from previous measures available (assuming no change for noncompleters). For per-protocol analysis, data from excluded subjects will be disregarded for analysis. The groups will be compared at baseline by the chi-square test for qualitative data and by the *t* test for quantitative data. To analyze changes in outcomes at baseline, post-treatment, and follow-up between and within groups, analysis of variance with repeated measures will be applied. A normality test will be applied to the outcome measures; when data are not normally distributed, equivalent nonparametric tests will be used. Potential interactions between treatment and covariates, such as age, sex, comorbidities, medications, dizziness features, psychocognitive aspects, adherences and follow-up data, will also be tested. The results will be presented as frequencies/percentages for categorical variables, and as means, medians, standard deviations and 95% confidence intervals for continuous variables. Data analyses will be performed using SPSS for Windows version 17.0 (SPSS Inc., Chicago, IL, USA) and the significance value for all tests will be set at *P* <0.05.

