**Discussion:**

Vestibular rehabilitation through the Cawthorne&Cooksey protocol has already proved to be effective. However, the addition of other components related to body balance control has been proposed to improve the rehabilitation of older people with chronic dizziness from vestibular disorders.

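### Carrying the last score forward is the only missing-data rule for the intention-to-treat comparison of DHI and DGI, and it can bias the difference in either direction

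*Protocol article*

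**What the plan says.** The Statistical analysis section sets the rule for the intention-to-treat analysis: "missing post-treatment or follow-up outcomes data will be replicated from previous measures available (assuming no change for noncompleters". The completed data then go into the main model: "analysis of variance with repeated measures will be applied". The only other analysis named is per-protocol: "For per-protocol analysis, data from excluded subjects will be disregarded for analysis". The Abstract makes intention-to-treat the basis for comparing the two protocols.

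Three other places bear on how the rule works in practice:

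- Interventions creates a route to missing data: "In the event of three (random or consecutive) absences during treatment, the subject will be excluded from the research and regarded as a withdrawal". The article does not say whether such participants are still assessed at 8 weeks or 3 months.
- Table 1 schedules DHI and DGI at baseline, 8 weeks and 3 months only.
- The Abstract says of the control treatment: "Vestibular rehabilitation through the Cawthorne&Cooksey protocol has already proved to be effective". Interventions rejects a placebo or untreated group on the same ground.

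**The concern.** The rule gives each noncompleter a change of zero from the last available score. With no primary-outcome visit during treatment, that score is the baseline for anyone who leaves before 8 weeks and is not assessed afterwards. Such a participant also counts automatically as not improved on the 18-point DHI and 4-point DGI thresholds.

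Zero change sits badly with a trial in which both arms are expected to improve. If noncompleters would have shared some of that improvement, each arm's mean is pulled towards baseline in proportion to its dropout. The estimated difference then reflects retention as well as treatment. Both primary outcomes are affected, and no planned analysis keeps all randomised participants under a different missing-data assumption.

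**Working it through.** **Plan's own figures.** Inputs from Sample size calculation: "34 individuals were required for the DGI (effect size = 2.5; standard deviation = 3.5"; "32 individuals for the DHI assessments (effect size = 14; standard deviation = 20"; "with 80% power, and 5% significance level". A two-sided two-sample t test gives 31.76, so 32 per group, for the DGI and 33.02, so 34 per group, for the DHI. The larger figure reproduces the total: 34 × 2 = 68. (The two per-outcome figures look interchanged. That is a separate matter and leaves the total unaffected.) Adding 15% gives 68 × 1.15 = 78.2, or about 39 per arm.

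**Formula.** Let δ be the true difference, C the mean improvement in the conventional arm, and d_c and d_m the dropout shares in the conventional and multimodal arms. Suppose noncompleters would have shared the full improvement of their arm and their baseline score is carried forward. The observed mean changes are then C(1 − d_c) and (C + δ)(1 − d_m), so

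expected estimate = δ + C(d_c − d_m) − δ·d_m.

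**Equal dropout d.** The expression reduces to δ(1 − d), whatever C is. At 15%:

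- DHI: 14 × 0.85 = 11.9
- DGI: 2.5 × 0.85 = 2.125

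Power was simulated with 39 per arm, a t test on change scores, SD 20 or 3.5, and dropout completely at random. Assumed improvements were 18 DHI and 4 DGI points, which are the article's own improvement thresholds. Carry-forward gave 0.71 (DHI) and 0.69 (DGI). Analysing the observed data gave 0.80 and 0.82. The extra 15% recruited replaces lost numbers but does not undo the dilution.

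**Unequal dropout, DHI, δ = 14, C = 20 (assumed).**

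| Conventional / multimodal dropout | Arithmetic | Expected estimate |
|---|---|---|
| 10% / 20% | 14 − 2.0 − 2.8 | 9.2 |
| 20% / 10% | 14 + 2.0 − 1.4 | 14.6 |
| 5% / 25% | 14 − 4.0 − 3.5 | 6.5 |
| 25% / 5% | 14 + 4.0 − 0.7 | 17.3 |

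**No true difference (δ = 0).** The expected estimate is C(d_c − d_m), and the arm with more dropout looks worse.

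- 10-point gap, C = 20: 20 × 0.10 = 2.0 DHI points. Simulated type I error was about 0.07.
- 20-point gap, C = 20: 20 × 0.20 = 4.0 points. Type I error was 0.124 (t test) and 0.165 (ANCOVA), and about 0.15 with repeated-measures ANOVA.
- DGI with C = 4: 0.4 and 0.8 points, with type I error 0.08 and 0.17.

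**Sensitivity to the assumptions.** For a 10-point gap, C = 9, 18 or 27 gives 0.9, 1.8 or 2.7 spurious DHI points. C = 0 gives none, and type I error stays at 0.05. If noncompleters would have had only a fraction f of their arm's improvement, the bias scales with f. At equal 15% dropout the DHI shortfall is f × 0.15 × 14, which is 2.1 for f = 1, 1.05 for f = 0.5 and 0 for f = 0.

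**The case against.** The best defence is that no change may be close to the truth for some noncompleters. Participants have dizziness that has already failed to compensate, the first two weeks of the conventional protocol cover only lying and sitting exercises, and the statements of efficacy concern the programme, not a partial course. This stands as a limit: the bias shrinks as f falls and vanishes at f = 0. The figures above give noncompleters the full benefit, which is itself a strong assumption. But the rule applies equally to someone withdrawn late in the 16 sessions, and the article gives no reason to expect zero change there.

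A second defence is that the per-protocol analysis leaves excluded subjects out, so a result without carry-forward for them will be available. It will, but that analysis selects on attendance after randomisation, so it is not an intention-to-treat answer under another missing-data assumption.

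A third is that the alternative performs well in the simulations only because dropout was generated at random. That is correct. If attendance tracks outcome, an observed-data analysis may be biased too, so the fix needs its own sensitivity analysis.

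A reader might also infer that standard errors are wrong because carried values are treated as observed. The check does not support this. With no true difference and 39 per arm, the mean model standard error and the empirical standard deviation were 4.47 and 4.49 at 15%/15% dropout, and 4.46 and 4.47 at 10%/20%. The excess rejections come from bias in the estimate.

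**Conclusion.** The concern holds in conditional form and should be fixed. The rule is stated in the article, applies to both primary outcomes, and conflicts with the improvement the trial expects in both arms. At equal 15% dropout it costs up to 2.1 of 14 DHI points and brings power to about 0.7. A 10-point gap gives about 2 spurious DHI points and a type I error of about 7%. The 12–17% type I error needs a 20-point gap, which nothing in the article suggests.

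These sizes rest on assumed within-arm improvement, assumed dropout, and noncompleters sharing their arm's improvement. They apply where baseline is carried forward. Where an 8-week score is carried to 3 months, the bias depends on change after treatment and can go either way.

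Two stronger readings are not supported. Carry-forward does not always shrink the effect: if the conventional arm loses enough more participants, the effect is preserved or enlarged, and the article does not say which arm will lose more. Nor does every dropout gap create a false difference: that needs a non-zero mean change that noncompleters would have shared.

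**What to change.** Replace the carry-forward sentence in Statistical analysis. The main intention-to-treat analysis should include all randomised participants in their assigned arm, by one of two methods:

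- a likelihood-based linear mixed model with baseline as covariate, using every observed post-baseline score, including any obtained after withdrawal; or
- multiple imputation by arm, using baseline and attendance.

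A participant with no post-baseline score adds no outcome information to the mixed model. If many leave before 8 weeks, imputation that uses attendance is the more informative choice.

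Keep carry-forward as a labelled sensitivity analysis beside a delta-adjusted one. Describe the per-protocol result as conditional on attendance. The article already aims to report withdrawals; specify that dropout is given by arm with reasons.

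The cost is a reworded passage and modest programming. No new data are needed: Trial status puts the end of the study at September 2012 and the outcome analysis in 2013. The downside is reliance on a missing-at-random assumption, which the delta-adjusted analysis is there to probe.

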### Randomization

Older individuals who meet the inclusion criteria following the baseline assessment and sign the informed consent will be randomized into one of two VR protocols: conventional or multimodal. Randomization will be accomplished by a statistical computer program, by blocks. The block randomization will be gradually performed during the study according to the number of eligible participants registered on the waiting list. Hence, the block sizes will not be fixed and will vary from 4 to 12 subjects, concerning the minimum and maximum capacity for VR at the Otoneurology outpatient clinic. Blocks will therefore eventually be composed of an odd number of participants, and as a consequence unequal groups could be formed. Block randomization was preferred in order to prevent time-related influences from disturbing the homogeneity of both groups over the data collection period (2 years and 6 months). Sample randomization and allocation will be performed by a researcher who is not involved in the clinical trial. In order to assure concealed allocation, the treating therapist will be informed by telephone call regarding the allocation of each participant just before their first session.

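### Baseline significance tests between the randomised groups are uninformative and a poor screen for imbalance; describe baseline instead and adjust DHI and DGI for their baseline values whatever is observed

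*Protocol article*

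**What the plan says.** In the protocol article, the Statistical analysis section states "The groups will be compared at baseline by the chi-square test for qualitative data", and for continuous variables the t "test for quantitative data". The same section closes with "the significance value for all tests will be set at" P <0.05, so that threshold covers the baseline tests too. It gives no purpose for these tests and no rule that acts on their result.

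The Outcome measures section places the baseline assessment before randomisation. The Randomization section describes computer-generated blocks, handled by a researcher outside the trial: "In order to assure concealed allocation, the treating therapist will be informed by telephone call" just before each participant's first session.

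Outcomes are to be analysed by repeated-measures ANOVA over baseline, post-treatment and follow-up, between and within groups. Covariates are mentioned only for tests of interaction with treatment. The article names no between-group comparison adjusted for the baseline value of the outcome.

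**The concern.** A test of two groups formed by concealed randomisation, on data collected beforehand, has a null hypothesis that is true by design. A small P value can then only be a chance finding, and a large one does not show that the arms are alike.

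What matters for a prognostic variable such as baseline DHI is how far apart the arms are and how strongly the variable predicts the outcome. A P value measures neither. A non-significant test can sit beside an imbalance that is large against the effect sought, and a significant one can fall on a variable of no importance. What is at stake is modest: baseline reporting that may mislead, and an outcome contrast that stays open to chance imbalance when data already collected could remove it.

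**Working it through.** **Inputs.** From Sample size calculation: DHI difference 14, SD 20; DGI difference 2.5, SD 3.5; 80% power, 5% level; minimum total 68; at least 15% more for dropout. Two-sided tests are assumed. The article calls the SDs population values; using them as baseline SDs is an assumption.

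**The plan's own sample size.** An exact two-sided t test needs 31.8, so 32 per arm, for DGI and 33.02, so 34 per arm, for DHI. The article states 34 and 32. The two figures look transposed, but the total of 2 × 34 = 68 is reproduced and nothing below depends on the order.

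**Number per arm at baseline.** The minimum is 34. With the dropout allowance, 68 × 1.15 = 78.2 or 68/0.85 = 80 are randomised, about 39 to 40 per arm. Both ends are shown.

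**Largest observed imbalance not flagged** = t(0.975, 2n−2) × SD × √(2/n).
- DHI, n = 34: SE = 20 × √(2/34) = 4.85; limit 9.7 points; 9.7/14 = 69%.
- DHI, n = 40: SE = 20 × √(2/40) = 4.47; limit 8.9 points; 8.9/14 = 64%.
- DGI, n = 34: SE = 0.85; limit 1.69 points; 1.69/2.5 = 68%.
- DGI, n = 40: SE = 0.78; limit 1.56 points; 1.56/2.5 = 62%.

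An observed DHI imbalance of 7 points, half the target, gives 7/4.85 = 1.44 at 34 per arm, P about 0.15, or 7/4.47 = 1.57 at 40 per arm, P about 0.12. It is not flagged. Chance alone produces an imbalance above 7 points in about 15% and 12% of randomisations respectively.

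**Expected chance differences** = 0.05 × number of tests. The article does not give the number, so it has to be counted from Outcome measures and Table 1.
- Only the 16 Table 1 rows measured at baseline: 0.05 × 16 = 0.8.
- Items named separately: 30 outcome-type items plus 14 characterisation items = 44; 0.05 × 44 = 2.2.
- Adding the DHI and VADL subscales and the cutoffs, about 53: 0.05 × 53 = 2.7.

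These expected counts do not require the tests to be independent.

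**What an imbalance does to the outcome contrast.** Let d be the observed baseline difference and ρ the baseline-outcome correlation, with equal variances. Given d, the expected difference at follow-up is (effect + ρd). The contrast of changes is therefore effect + ρd − d = effect − (1−ρ)d: a shift of (1−ρ)d in the direction opposite to the imbalance. The article gives no ρ; 0.3 to 0.7 is assumed.
- d = 7, ρ = 0.7: 0.3 × 7 = 2.1 points, 15% of 14.
- d = 7, ρ = 0.3: 0.7 × 7 = 4.9 points, 35% of 14.

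Adjustment for baseline removes this shift. It also improves precision: for one follow-up time the variance is proportional to 1−ρ², against 2(1−ρ) for change, a ratio of (1+ρ)/2, or 0.65 to 0.85 over the same range of ρ.

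**The case against.** The strongest reply is that nothing in the plan hangs on these tests. No covariate is chosen, no model changed and no failure of randomisation declared on a baseline P value, so deleting the P values would alter no treatment result. That stands, and it is why the point is minor.

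Several stronger readings are tempting, and the article does not support them:
- A reader might infer that the analysis ignores baseline altogether. It does not: baseline is a time point in the repeated-measures ANOVA, so the group-by-time comparison is one of changes.
- A reader might infer that an unflagged 9.7-point imbalance distorts the DHI result by two thirds of the target. Only the fraction (1−ρ) carries over, and over repeated randomisations the shift averages to zero.
- A reader might quote the test's power against a true baseline imbalance. Under randomisation there is no true non-zero difference; only the observed one is meaningful.
- A reader might state flatly that about two false differences will appear, or that at least one is nearly certain. The first depends on an unstated count, the second on independence among plainly related items such as the TUG versions and the static balance conditions.
- A reader might take the tests to be the plan's check of homogeneity. That word belongs to the reason for blocking: "Block randomization was preferred in order to prevent time-related influences from disturbing the homogeneity of both groups". The plan also already provides for descriptive summaries.

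It can also be said that an adjusted comparison may stand in an analysis plan that is not shown. If so, that half of the fix is already in place; the baseline tests themselves are fixed in the article.

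**Conclusion.** The point holds as a minor one. For the groups as randomised, the baseline tests address a null that is true by design, provided randomisation was carried out as described. As a screen they pass observed DHI imbalances up to about 9 to 9.7 points (64% to 69% of the target) and are expected to produce 0.8 to 2.7 chance differences. The substantive gain lies in the outcome comparison: a contrast of changes keeps a shift of (1−ρ)d, 2.1 to 4.9 DHI points for a 7-point imbalance, which baseline adjustment would remove.

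These figures assume SD 20 at baseline, two-sided tests, 34 to 40 per arm, equal variances, and ρ between 0.3 and 0.7. The argument does not extend to a baseline comparison within the per-protocol set, because those exclusions follow randomisation.

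**What to change.** In Statistical analysis:
- Remove the chi-square and t tests of the groups as randomised. Show baseline data by arm with n, means and SDs (medians where suited), and frequencies with percentages.
- State, before outcomes are analysed, that the between-group comparisons of DHI and DGI at post-treatment and follow-up adjust for the baseline value of the outcome, by ANCOVA or an equivalent longitudinal model, whatever imbalance is seen.
- State that no covariate is chosen by a baseline P value.

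The cost is a few sentences. Baseline DHI and DGI are already collected, the sample size is unchanged, and the baseline table takes less work.
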